# Effects of shared medical appointments on quality of life and cost-effectiveness for patients with a chronic neuromuscular disease. Study protocol of a randomized controlled trial

**DOI:** 10.1186/1471-2377-11-106

**Published:** 2011-08-23

## Abstract

**Background:**

Shared medical appointments are a series of one-to-one doctor-patient contacts, in presence of a group of 6-10 fellow patients. This group visits substitute the annual control visits of patients with the neurologist. The same items attended to in a one-to- one appointment are addressed. The possible advantages of a shared medical appointment could be an added value to the present management of neuromuscular patients. The currently problem-focused one-to-one out-patient visits often leave little time for the patient's psychosocial needs, patient education, and patient empowerment.

**Methods/design:**

A randomized, prospective controlled study (RCT) with a follow up of 6 months will be conducted to evaluate the clinical and cost-effectiveness of shared medical appointments compared to usual care for 300 neuromuscular patients and their partners at the Radboud University Nijmegen Medical Center. Every included patient will be randomly allocated to one of the two study arms. This study has been reviewed and approved by the medical ethics committee of the region Arnhem-Nijmegen, the Netherlands. The primary outcome measure is quality of life as measured by the EQ-5D, SF-36 and the Individualized neuromuscular Quality of Life Questionnaire. The primary analysis will be an intention-to-treat analysis on the area under the curve of the quality of life scores. A linear mixed model will be used with random factor group and fixed factors treatment, baseline score and type of neuromuscular disease. For the economic evaluation an incremental cost-effectiveness analysis will be conducted from a societal perspective, relating differences in costs to difference in health outcome. Results are expected in 2012.

**Discussion:**

This study will be the first randomized controlled trial which evaluates the effect of shared medical appointments versus usual care for neuromuscular patients. This will enable to determine if there is additional value of shared medical appointments to the current therapeutical spectrum. When this study shows that group visits produce the alleged benefits, this may help to increase the acceptance of this innovative and creative way of using one of the most precious resources in health care more efficiently: time.

**Trial registration:**

DutchTrial Register http://www.trialregister.nlNTR1412

## Background

### Introduction

As of January 2006, the department of neurology at the RUNMC has started offering shared medical appointments or group visits to patients with a neuromuscular disease. This novel approach of delivering outpatient care is now being compared with usual care during a randomized controlled trial with 300 patients and their partners. The focus in this trial is on health outcomes and costs.

### Motive

Most neuromuscular diseases are chronic progressive diseases necessitating periodic specialized care. Because of the progressive nature of the disease, existing symptoms aggravate over time and new symptoms may develop over time, requiring adjustment of management, and giving rise to new questions on the part of the patient and his or her partner. In the absence of definitive cures for chronic neuromuscular diseases, the improvement of quality of life, patient- and partner satisfaction with care, self management and functional capacity become key objectives of care. Currently, these patients attend the out-patient clinic at regular intervals (usually annually), where they are seen in one-to-one patient- physician encounters. It is difficult, however, to fulfill the complex needs of neuromuscular patients in these brief, problem-focused out-patient visits which leave little time for the patient's psychosocial needs, patient education, and patient empowerment. The possible advantages of a shared medical appointment could be an answer to these questions. Our hypotheses are that shared medical appointments show 1) the same effect on the development of the disease as individual appointments 2) an improvement of self-efficacy as opposed to individual appointments, therefore resulting in an improved quality of life 3) better use of resource utilization and 4) a positive effect on self efficacy and quality of life of the partner as well as on the relationship [1-6].

### What is a shared medical appointment?

During a shared medical appointment or group visit, 6-10 patients and their partners are seen simultaneously by a physician who is supported by a group mentor. Shared medical appointments are a series of one on one doctor-patient contacts, in presence of a group fellow patients. A group visit takes 1,5 - 2 hours and substitutes the annual control visit of the patients. The same items the neurologist attends to in a one to one appointment are addressed. The physician has more time to give information and patients and partners can ask questions to- and learn from their fellow patients. The group mentor facilitates the group process, fosters interaction between patients and manages time. Shared medical appointments should not be confused with group education or peer support groups. As opposed to a group visit, these meetings do not substitute for the periodic consultation with the clinician [7,8].

Experience with shared medical appointments in patients with diabetes, heart failure, bone marrow transplantation and chronically ill older patients have been reported [9-14]. Evidence of group visits for neurological patients is at this moment at the level of a feasibility trial for patients with Parkinson disease [15].

## Methods/design

A randomized, prospective controlled study (RCT) with a follow up of 6 months will be conducted to evaluate the clinical and cost-effectiveness of shared medical appointments compared to usual care for neuromuscular patients. The trial flow of the proposed subject enrolment and randomization procedures are shown in Figure 1.

**Figure 1 F1:**
[figure not shown]
**flowchart of trial design**. CRAMP database: Computer Registry of All Myopathies and Polyneuropathies. INQOL: Individualized Neuromuscular Quality of Life.

### Study population

The aim is to include 270 evaluable patients with one of the following chronic neuromuscular diseases:

- Myotonic Dystrophy type 1 genetically determined (classic and juvenile type) [16];

- McArdles disease, Glycogen Storage Disease Type V. Biochemically and genetically determined;

- Facioscapulohumeral Muscular Dystrophy (FSHD), genetically determined;

- Chronic progressive external ophthalmoplegia (CPEO) as defined by Emery [17];

- Oculopharyngeal Muscular Dystrophy (OPMD), genetically determined;

- Inclusion body myositis (IBM) as defined by Badrising and Verschuuren [18,19]

- Non-dystrophic myotonias. These skeletal muscle channelopathies include two main groups: the chloride and sodium channelopathies [20];

- Myositis: Dermatomyositis and Polymyositis [21]

- Polyneuropathy: CMT1 and HNPP [22]

The partners of these patients will also be included. All patients will be identified by CRAMP, a neuromuscular database containing data from over 4500 patients with neuromuscular disease attending the outpatient clinic of the Radboud University Nijmegen Medical Center [23]. From this database, patients who meet the inclusion criteria (table 1) will be contacted by telephone by the primary investigator (FS) to inform them about the study and ask permission to send information and informed consent forms. If the patient decides not to participate in the study, the reason will be asked and documented. If written consent forms are not returned within 3 weeks, patients will receive a reminder phone call. After written informed consent is obtained, patients and their partners are randomized to one of the two study arms. Reasons for drop-out will be asked and documented.

**Table 1 T1:** inclusion and exclusion criteria

Inclusion criteria	
1.	Registered in CRAMP database with one of the following neuromuscular diseases

	➢ Myotonic Dystrophy type 1. genetically proven (classic and juvenile type)

	➢ McArdles disease, Glycogen Storage Disease Type V. Biochemically and genetically proven

	➢ Facioscapulohumeral Muscular Dystrophy (FSHD). genetically determined

	➢ Chronic progressive external ophthalmoplegia (CPEO) as defined by Emery

	➢ Oculopharyngeal Muscular Dystrophy (OPMD). genetically determined

	➢ Inclusion body myositis (IBM)as defined by Badrising and Verschuuren.

	➢ Non-dystrophic myotonias. These skeletal muscle channelopathies include two main groups: the chloride and sodium channelopathies.

	➢ Myositis: Dermatomyositis and Polymyositis

	➢ Polyneuropathy: CMT1 & HNPP

2.	Age > 18 years

3.	Patients and their partners are control patients in care at the department of neurology RUNMC

**Exclusion criteria**	

1.	Patients or partners with severe hearing problems

2.	Patients or partners who cannot speak, read or understand the Dutch language well

3.	Patients and their partner who have had a control visit with a neurologist at the neurology department of the RUNMC less than 6 months ago

### Ethical approval and registration

This study has been reviewed and approved by the medical ethics committee of the region Arnhem-Nijmegen, the Netherlands. (reference CMO nr. 2008/224) and has been registered in the NTR (Dutch Trial Registration nr NTR1412) Patients and their partners receive verbal and written information about the study and written informed consent will be obtained before randomization.

### Randomization and blinding

Concealed randomization will be performed through computer-generated randomization software. Every included patient will be randomly allocated to one of the two study arms by the computer. The method of simple randomization is applied. In view of the nature of the interventions, blinding of the participants, participating neurologists and primary researcher is not possible. The statistician who conducts the analysis of the data will, however, be blinded for the patients' groups.

### Interventions

Care as usual: individual outpatient appointment.

Patients and partners who are randomized to the control group will have their regular control visit with one of the participating neuromuscular neurologists at the outpatient neurology department of the RUNMC. This one on one control visit substitutes the regular annual control visit the patients pay to the neurology department. The same items that are normally attended to during the control visit, are attended to by the neurologist. All physical examinations, prescriptions and referrals are conducted as deemed appropriate, and documented in the patient record. The regular one on one control visit takes 30 minutes.

Intervention: shared medical appointment

Patients and partners who are randomized to the intervention arm of the study will be invited to a shared medical appointment of 1,5 - 2 hours with one of the participating neuromuscular neurologists and a group mentor at the outpatient neurology department of the RUNMC. The same neurologists execute the individual appointments and the shared medical appointments. As well as for the individual appointments, the shared medical appointments substitute for the annual control visit of the patients. The same items the neurologist attends to in a one on one control visit are attended to during the shared medical appointment. The neurologist is supported by a group mentor, who facilitates the group process, fosters interaction between patients and manages time.

The group mentor starts with a short introduction in which the process of the shared medical appointment is explained and confidentiality is emphasized. Patients and their partners are asked to fill out a privacy form, which is kept in the patient's records, in order to emphasize the confidentiality of the group visit. If physical examinations are deemed necessary, they are conducted in a private examination room close to the group visit room directly after the shared medical appointment. Necessary prescriptions, referrals, and chart notes are being taken care of during or directly after the shared medical appointment. The neurologists have received training in conducting shared medical appointments prior to the study. The process of the shared medical appointments is described in appendix 1.

### Compliance and attrition

When participants indicate that they wish to discontinue their participation in the study, reasons will be documented.

### Outcomes

Outcome measures for patients are listed in table 2. The primary outcome measure is quality of life (daily activity limitations, pain, mood, fatigue, social activities) as measured by the EQ-5D, SF-36 and the Individualized neuromuscular Quality of Life Questionnaire (INQoL). For the SF-36 and EQ 5 D, normative scores are available based on the Dutch population. For the INQoL, no Dutch version was available. With granted authorization from the authors, a translation into the Dutch language was made [24-27]. Secondary outcome measures are (1) Use of health care resources (use of health care services, medication, compliance with medication, use of assistance with daily activities) Questions from the Client Service Receipt Inventory (CSRI) are used to record service utilization [28]. (2) Self efficacy (how much confidence one has in being able to execute specific behaviour), as measured by the Self Efficacy questionnaire from Schwarzer [29]. This is a 10-item psychometric scale that is designed to assess self-beliefs to cope with a variety of difficult demands in life. Also, a questionnaire to measure self efficacy of patients with neuromuscular disease was developed by the research group. (3) The need for social support was assessed by using the subscale emotional support of the Dutch questionnaire SSLD (Sociale Steun Lijst-Discrepanties) from Sanderman and van Sonderen [30]. (4) Satisfaction with relationship was measured by asking the participants to rate their relationship on a 1/10 scale and to rate their relationship on a VAS scale, ranging from the worst possible relationship to the best possible relationship [31] (5) Satisfaction with and aspects of the visit, as measured by The QUality Of care Through the patient's Eyes (QUOTE) questionnaire [32]. The severity of the disease as measured through the Rankin-scale is assessed during the shared medical appointments and through reviewing the chart notes for individual appointments by the participating neurologists or primary researcher [33,34].

**Table 2 T2:** Outcome measures and instrumentation patients

	Instruments	T0	T1	T2	T3

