**Primary outcome measures**					

Quality of life	EQ5D, SF36, INQOL	√	√	√	√

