### Statistical analysis

#### Sample size

On the basis of the literature [37,38] group visits may be expected to lead to a clinically relevant improvement in quality of life of 5 points on the total SF-36 score. Assuming a standard deviation of 12 [39], 92 patients need to be enrolled in both groups to achieve a statistical power of 80% (alpha = 0.05, two-sided). Taking into account non-evaluable patients, to adjust for imbalances and to be able to do subgroup analysis on age, sex, gender and severity, 135 patients will be enrolled in both groups. In order to be able to evaluate 270 patients, the aim is to include 300 patients.

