#### Analysis of outcome measures

300 neuromuscular patients and if applicable their partners will be included in the study. The primary analysis will be an intention-to-treat analysis on the area under the curve of the quality of life scores (average response during 6 months). A linear mixed model will be used with random factor group and fixed factors treatment, baseline score and type of neuromuscular disease. Other outcome parameters will be evaluated in a similar way and additional per protocol analyses will be carried out.

For the analyses SPSS version 17 statistical software will be used. A p-value of 0.05 will be considered statistically significant. Missing data will be imputed using multiple imputation techniques.

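### Three unranked primary instruments and no success rule, while the stated 5% alpha and 80% power were derived for the total SF-36 score only

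*Protocol article*

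**What the plan says.** - **Outcomes** (protocol article): the primary outcome is quality of life, "social activities) as measured by the EQ-5D, SF-36 and the Individualized neuromuscular Quality of Life Questionnaire (INQoL"). The primary row of Table 2 lists "EQ5D, SF36, INQOL" at all four time points, and the Abstract names the same three. None is marked as leading.
- **Analysis of outcome measures**: "The primary analysis will be an intention-to-treat analysis on the area under the curve of the quality of life scores", with scores in the plural and no instrument named. The only decision criterion is "A p-value of 0.05 will be considered statistically significant".
- **Sample size**: the target is a "clinically relevant improvement in quality of life of 5 points on the total SF-36 score". The other inputs are "Assuming a standard deviation of 12", 80% power and "alpha = 0.05, two-sided", giving 92 per group. This is raised to 135 per group for non-evaluable patients, imbalances and subgroup analyses, and 300 patients are to be included to yield 270 evaluable.
- **Economic evaluation** (under Statistical analysis): health outcome is measured by the EQ-5D, while the trial's primary outcome is again called just quality of life.

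**The concern.** The article fixes three things that do not fit together: a primary outcome with three equal instruments, one 0.05 threshold, and a sample size for one score from one instrument. Nothing links them, whether a hierarchy, a composite, a division of alpha, or a statement of how many instruments must be positive.

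If the instruments disagree, for example EQ-5D significant and SF-36 not, the plan does not say whether the trial succeeded, and that decision could be made after the results are known. The error rate behind a positive claim, or the power to reach one, would then differ from the stated 5% and 80%. The economic evaluation inherits the ambiguity. It falls back on cost minimisation when effects do not differ significantly, so mixed results across instruments would leave that trigger open too.

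**Working it through.** **Inputs from the article.** Difference 5, SD 12, two-sided alpha 0.05, power 80%, 92 per group required and 135 per group planned (Sample size); three primary instruments (Outcomes, Table 2). **Assumed.** One score per instrument, and equal pairwise correlation r between the three test statistics. The article gives no correlation, so a range is shown. Clustering by group visit is left out, as in the article's own calculation.

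**1. The stated sample size.** n per group = 2(z₀.₉₇₅ + z₀.₈₀)² / (5/12)² = 2(1.960 + 0.842)² / 0.1736 = 90.4, so 91. The t-test version gives 91.4, so 92. The article's 92 reproduces: it is right for one SF-36 score at unadjusted 0.05.

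**2. If any one of three suffices.** With independent tests the family-wise error is 1 − 0.95³ = 14.3%. With correlated tests it is 1 − P(all three |Z| ≤ 1.96) for equicorrelated normal statistics:

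| r (assumed) | Family-wise error |
|---|---|
| 0 | 14.3% |
| 0.3 | 13.6% |
| 0.5 | 12.5% |
| 0.7 | 10.9% |
| 0.8 | 9.8% |
| 0.9 | 8.4% |

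These values are from numerical integration; a simulation with 1,000,000 draws per correlation agrees to within 0.1 percentage points.

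**3. If all three are required.** A false joint claim needs significance on at least one instrument with no true effect, so type I error cannot exceed 5%. Joint power cannot exceed the lowest of the three individual powers. As an illustration only, suppose EQ-5D and INQoL had the same standardised effect as the SF-36. At 92 per group joint power would lie between 0.80³ = 51% (independent) and 80% (perfectly correlated). At 135 per group the range would be 0.928³ = 80% to 93%. The article gives no effect or SD for the other two instruments, so the true joint power is unknown.

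**4. One primary endpoint, SF-36 at 0.05.** Power = Φ((5/12)√(n/2) − 1.960). At n = 92: Φ(2.826 − 1.960) = 81%. At n = 135: Φ(3.423 − 1.960) = 93%.

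**5. Three instruments under Holm.** The strictest step is 0.05/3 = 0.0167, critical value 2.394. The SF-36 then needs 2(2.394 + 0.842)² / 0.1736 = 120.6, so 121 per group (t-test 122.05, so 123). Power at 135 is Φ(3.423 − 2.394) = 84.8% (t-test 84.4%). At 92 it is Φ(2.826 − 2.394) = 67%.

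**The case against.** A reader might infer that each instrument is tested separately at 0.05, that any one of them suffices, and hence that the trial's error rate is well above 5%. The article does not say so. Its 0.05 is a general threshold and no success rule is attached to it. This objection stands: the inflation in step 2 is conditional on one reading, and under the all-three reading there is none.

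A reader might also enlarge the family with the partners' EQ-5D from Table 3, or with separate tests of SF-36 and INQoL subscales. Neither is supported. Partners are a different population with their own table and their own hypothesis, and nothing makes a partner result a success on the patient question. No section proposes subscale tests, and the sample size uses a total score.

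The independence figure of 14.3% is an upper end. Three questionnaires on the same construct in the same patients are likely to be correlated, and at 0.7 to 0.9 the figure is about 8% to 11%.

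It can also be said that the sample size points to the SF-36 as the lead measure, that EQ-5D has its own role in the economic evaluation, and that multiplicity detail may sit in an analysis plan not shown here. This helps only in part. Sizing on a score does not rank it, and the Abstract, Outcomes and Table 2 put all three on an equal footing. An alpha rule elsewhere would not remove the mismatch between the primary outcome and the sample-size basis that the article itself states.

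**Conclusion.** The point holds as a mismatch, not as a demonstrated inflation of error. The article names three unranked primary instruments, gives no rule for success, and supports its alpha of 0.05 and 80% power for the total SF-36 score only. Under an any-of-three rule the family-wise error is about 8% to 14% rather than 5%, for one score per instrument and assumed correlations of 0.9 down to 0. Under an all-three rule type I error stays at or below 5%, but joint power was never planned. On neither reading do both stated figures describe the primary claim. The sample-size arithmetic itself is correct. Confidence is high in the mismatch; the size of any inflation depends on a rule and a correlation that the article does not give.

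**What to change.** **Preferred.** Name one primary endpoint: the 6-month AUC of the total SF-36 score to which the 5-point difference and SD 12 apply, tested at two-sided 0.05. Make EQ-5D and INQoL secondary, with EQ-5D keeping its role in the economic evaluation. The 92 per group then remains valid, with about 93% power at 135 per group. The cost is that a significant EQ-5D or INQoL result alone no longer counts as primary success.

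**Alternative.** Keep all three instruments, test them by Holm at 0.05 overall, state that any instrument significant under that procedure counts, and restate the power. At the strictest step the SF-36 needs 121–123 per group, and 135 per group gives about 84–85%. The cost is somewhat lower power, and use of a margin that the sample-size section set aside for non-evaluable patients, imbalances and subgroup analyses.

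Either option is a change of wording in the Abstract, Outcomes, Table 2 and the analysis section, made before database lock. No new data are needed.
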